### Outcome measures

Outcome data will be provided by three different kinds of observers: blinded research assistants, parents/carers and teachers.

#### Blinding of outcome data collection

Research assistants will be blind to group allocations when collecting the quantitative outcome measures listed below. They will have received relevant training from the research team. All research assistants will have an enhanced Disclosure and Barring Service (DBS) check and undergo relevant safeguarding and data protection training. When a research assistant visits a school to administer the assessments, teachers and teaching assistants at the school will be reminded on every visit not to reveal allocation to the research assistants. Any instances of unblinding during the assessments will be recorded (using a bespoke unblinding form which will include information on who was unblinded, the source of unblinding, and the reason for unblinding) and the unblinded research assistant will be replaced with another research assistant who is blind. Research assistants will also collect qualitative data from schools; for this data, they will not be blinded. Hence, each school will be allocated both a blinded and unblinded research assistant.

Teachers and parents/carers will be requested to complete outcome measures for Focal children. Whilst blinded during the completion of these outcome measures at baseline, due to the nature of the intervention, it is not possible for them to be blinded at 15–20- or 35–40-weeks post-tests.

#### Primary outcome

The primary outcome is the Focal children’s pragmatic language ability measured using the validated Test of Pragmatic Skills (TPS [26]). This assessment will be administered by a blinded research assistant at baseline, and at 15–20- and 35–40-weeks post-randomisation. The measurement at 35–40 weeks will serve as the primary endpoint for the trial, with the 15–20-week measurement being a secondary outcome.

#### Secondary outcomes

The following secondary outcome measures will also be administered to Focal children by a blinded research assistant at baseline, 15–20 weeks, and 35–40 weeks post-randomisation.Clinical Evaluation of Language Fundamentals-5 (CELF-5 [27])—Recalling Sentences and Following Directions subscales.Expression, Reception and Recall of Narrative Instrument (ERRNI [24]) assesses the ability to relate, comprehend and remember information after a short delay.Droodles Tasks and Communication Test [28, 29].

The Droodles Task and Communication Test are a series of tasks and puzzles testing children’s ability to evaluate the effects of ambiguous versus informative communications, a key skill targeted by E-PLAYS. The tests are embedded in play sessions with dolls and puppets and have previously been used for this age group.

The battery of assessments above will take approximately 50 min to administer per child at each data collection time-point. The children’s tests are mostly tasks presented as fun games to play and therefore not onerous for the children. These tests can be divided into two or more sessions as the children are very young and may tire.

The following secondary outcome measures (relating to health-related quality of life) will be completed by Focal children’s parents/carers at baseline, 15–20 weeks and 35–40 weeks post-randomisation:Child Health Utility (CHU-9D), paediatric generic preference-based measure of quality of life. The CHU-9D includes specific dimensions on school and joining in with activities [30, 31].EQ-5D-Y (proxy version 1). This is a widely used standardised generic measure of health-related quality of life for younger children [32].Resource use data: A bespoke questionnaire (developed for the E-PLAYS feasibility study [17]) will collect resource use data about healthcare, voluntary organisations and educational resources.

We anticipate that it will take parents/carers approximately 30 min to complete the questionnaires at each data collection time-point.

The following secondary outcome measures will be completed by the Focal children’s teacher at baseline, 15–20 weeks and 35–40 weeks post-randomisation; these measures are completed by the teachers without the child present:Children’s Communication Checklist-2 (CCC-2[33]). CCC-2 is a standardised questionnaire of children’s communication impairment.The Strengths and Difficulties Questionnaire (SDQ [34]). The SDQ is widely used as a mental health indicator with subscales assessing behavioural, emotional and peer problems.

We anticipate the questionnaires listed above will take teachers no longer than ten minutes per child to complete at each data collection time-point.

The following secondary outcome measures will be administered to a randomly selected subgroup of 88 Partner children (1 per school) in school by a research assistant at baseline, 15–20 weeks and 35- 40 weeks post-randomisation:

Partner children’s pragmatic language ability measured using the validated TPS [26].

### Sample size calculations

#### Original

We will recruit single- and multi-form entry schools. Pupils will be recruited from Years 1 and 2; assuming an average of two classes per year, based on our feasibility study [17] we expect to identify a mean of ten eligible Focal children per school, of which six will consent and be recruited. The intervention will be delivered to the participating children by teaching assistants and we expect an average of 1.5 teaching assistants per class.

In multi-form entry schools, we will have clustering of classes within year groups, but in one-form entry schools the levels of class and year will be equivalent. We consider that in multi-form entry schools the difference in clustering between class and year will be negligible so we shall ignore the level of class. Therefore, this cluster randomised trial assumes a three-level structure in that pupils (level 1) are nested within year group (level 2) nested within schools (level 3). Randomisation will take place at school-level. The year groups participating in this trial are consecutive (Years 1 and 2) so the difference between them will be minimal and the cluster effect of school will likely dominate the effect of class; therefore, we have not explicitly accounted for clustering at the class level in this sample size calculation. The largest influence within schools is likely to be between teaching assistants since these will be the ones delivering the intervention to the children; however, in most schools we expect that the ratio of teaching assistants to participating children will be approximately 1:1 so this level of clustering is eliminated. In the feasibility trial [17], the school-level ICC was small (< 0.01); here we have assumed a conservative ICC of 0.05 at the school-level to account for all levels of potential clustering.

In our feasibility trial the standard deviation (SD) of the primary outcome measure, the TPS [26], at baseline was 7.2 (95% CI 5.4 to 9.7) and the observed correlations between the TPS score at baseline and the scores at weeks 15–20 and 35–40, respectively, were 0.84 (95% CI 0.71 to 0.91) and 0.79 (95% CI 0.63 to 0.89). In the calculation for this trial we assume: a SD of 7, an ICC of 0.05 at the school-level, a mean cluster size of six (Focal children per school, at randomisation), 20% pupil level attrition at follow-up and a more conservative pre-post correlation of 0.6. To detect a difference in TPS score of 2 points (a third of a year’s progress based on the standardisation sample given in the TPS manual), with 90% power and a two-sided alpha of 5%, we would require 84 schools (504 focal children).

We will undertake an exploratory analysis to assess the potential impact of the intervention on Partner children’s (i.e., those who do not have social communication difficulties) pragmatic language skills. We will randomly select one Partner child from each school to complete the TPS [26] at baseline, at 15–20 weeks post-randomisation and at 35–40 weeks post-randomisation with a blinded, independent research assistant. This will allow for a comparison of the outcomes in these typically-developing children between intervention (where the child will partner a participating Focal child in E-PLAYS) and control schools (care as usual).

Since this is an exploratory analysis, we have planned the sample size of one typically-developing child from each school for logistical reasons. Collecting the TPS [26] from only one extra child per school will not substantially increase the time or burden to complete outcome measures. Assuming a SD of 7, a pre- post-test correlation of 0.6 and 20% attrition, a sample size of 84 children (one per school) will give 80% power to detect a difference of 3.9 points in the TPS [26]. We shall compare TPS [26] scores of the typically developing children.

#### Revised

For the 20 school clusters recruited as part of the internal pilot phase, the observed mean cluster size (at randomisation) was 4.55 participants per cluster, around 25% less than the anticipated six participants per cluster detailed in the previous section.

Following discussion with the funder, the total target number of school clusters was changed to 88. Assuming a mean cluster size (at randomisation) of 4.55 and keeping all assumptions the same as previously (e.g.$$\delta$$ = 2, SD = 7, pre-post correlation = 0.6, school level intra-cluster correlation of 0.05 and 20% participant level attrition), 44 clusters per group would provide approximately 85.2% power for a two sided test of $${H}_{0}:\delta =0$$ (where $$\delta$$ is the difference in expected TPS score at 35–40 weeks).

As per the original proposal we will randomly select one Partner child per school to complete the primary outcome (TPS [26],) at baseline and 15–20- and 35–40-weeks post-randomisation. Under the same assumptions as before, a sample size of 88 children (one per school) will give 80% power to detect a difference of 3.4 points in the TPS [26].

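### The revised detectable difference for Partner children (3.4 points) does not follow from the stated assumptions, which give about 3.8 points; power at 3.4 is about 71%, not 80%

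*Protocol article*

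**What the plan says.** The protocol gives two detectable differences for the exploratory TPS comparison in Partner children, one child per school.

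- **Sample size calculations, Original.** The inputs are SD 7, 20% attrition and a pre-post correlation of 0.6. On these, the text says that "a sample size of 84 children (one per school) will give 80% power to detect a difference of 3.9 points".
- **Sample size calculations, Revised.** The number of schools rises from 84 to 88, and the number of Partner children with it. The text introduces the new figure with "Under the same assumptions as before" and states that "a sample size of 88 children (one per school) will give 80% power to detect a difference of 3.4 points".

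The Revised part also lists 20% participant-level attrition among the assumptions kept for the Focal-child calculation, so nothing there suggests that attrition was meant to be dropped.

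**The concern.** With SD, correlation, attrition, alpha and power all fixed, the detectable difference depends only on the number of children. An increase from 84 to 88 is 4.8%, yet the stated difference falls from 3.9 to 3.4, about 13%. A fall of that size needs (3.9/3.4)² = 1.32 times as many children, roughly 111 instead of 88.

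At stake is the sensitivity that the protocol claims for the question of whether taking part affects the typically developing classmates. A reader who takes 3.4 points at face value will believe that the revision improved this comparison by half a point, when the real gain is about 0.1 point. The reader will also take the chance of missing a true 3.4-point effect to be 20%, when it is about 29%.

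**Working it through.** **Inputs**

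- SD 7, correlation 0.6, attrition 20%, power 80%: the original Partner calculation.
- Two-sided alpha 5%: stated for the Focal calculation ("with 90% power and a two-sided alpha of 5"%) and assumed to apply to Partners too.
- Equal allocation, 44 schools per arm: the Revised part ("44 clusters per group would provide approximately 85.2% power").
- No design effect: there is one child per school, and the Partner analysis section drops the school random intercept for that reason.

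**Formula**

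The SD after adjustment for baseline is 7 × sqrt(1 − 0.6²) = 7 × 0.8 = 5.6.

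With n analysed per arm, the detectable difference by the normal approximation is (1.960 + 0.842) × 5.6 × sqrt(2/n). The t-based version solves for 80% power under the noncentral t distribution with 2n − 2 degrees of freedom.

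**Step 1: reproduce the original 3.9**

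84 × 0.8 = 67.2 analysed, 33.6 per arm.
- Normal: 2.802 × 5.6 × sqrt(2/33.6) = 3.83.
- t: 3.89, which rounds to the stated 3.9. Power at 3.9 is 80.3%.

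**Step 2: the revised figure on the same assumptions**

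88 × 0.8 = 70.4 analysed, 35.2 per arm.
- Normal: 2.802 × 5.6 × sqrt(2/35.2) = 3.74.
- t: 3.79.
- Power at 3.4 points: 70.9% (t) or 72.1% (normal).

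**Step 3: cross-check without a model**

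3.9 × sqrt(84/88) = 3.9 × 0.977 = 3.81. Allowing for rounding in the stated 3.9 (3.85 to 3.95), the range is 3.76 to 3.86. No value in it is near 3.4.

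**Step 4: where 3.4 comes from**

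| Variant for 88 children | Normal | t |
|---|---|---|
| 20% attrition, as stated | 3.74 | 3.79 |
| No attrition (44 per arm) | 3.34 | 3.38 |
| Attrition applied as 88/1.2 | 3.66 | 3.71 |
| SD not adjusted for baseline, 20% attrition | 4.68 | 4.74 |
| Change-score SD, 20% attrition | 4.18 | 4.24 |

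Only the no-attrition row fits: 3.38 rounds to 3.4, by the same t method that reproduces 3.9 with attrition. A one-sided 5% test with attrition gives 3.32 (normal), but it gives 3.40 for the original 84 children and so fails the 3.9 benchmark.

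**Step 5: the neighbouring Focal figure**

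4.55 × 0.8 = 3.64 analysed per school. The design effect is 1 + 2.64 × 0.05 = 1.132, and the effective n per arm is 44 × 3.64 / 1.132 = 141.5. Power for 2 points is 85.2% (normal), as stated. Without attrition it would be about 91%. Attrition was therefore applied to the Focal figure in the same part of the protocol.

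**Step 6: children needed for 3.4 points**

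- Normal: 43 analysed per arm, 86 / 0.8 = 107.5, so 108.
- t: 44 analysed per arm, 88 / 0.8 = 110.

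**The case against.** The arithmetic was not disputed; the objections concern weight and wording.

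- **Little depends on the figure.** The protocol calls the Partner comparison exploratory and says its size was chosen for logistical reasons. The 3.4 was derived from the sample size, not the reverse. No recruitment target, Focal analysis or decision rule uses it. This stands.
- **A null result will be judged on its confidence interval.** The statistical analysis section commits to point estimates with 95% intervals for Partner as well as Focal children, and nowhere proposes to read a null result against 3.4. This also stands. The harm is a claimed sensitivity about 0.4 points too favourable, not a built-in misinterpretation of the result.
- **The cause is not shown.** Omitted attrition fits and is the only variant tried that does, but a typing error cannot be excluded. This is fair, and the finding does not depend on the cause.
- **The corrected value depends on the method.** The protocol names no method for this calculation and gives no alpha specific to it. The normal approximation gives 3.7 and 72%, the t method 3.8 and 71%. The t method is preferred because it matches the protocol's own 3.9. Neither gives 3.4.

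**Conclusion.** The stated 3.4 points is wrong on the protocol's own assumptions and contradicts the 3.9 points given for the original sample. With SD 7, correlation 0.6, 20% attrition, two-sided 5% alpha and equal arms, 88 Partner children give 80% power for about 3.8 points. The stated value is about 10% too optimistic (3.4 against 3.79), and power at 3.4 points is 71 to 72%. The conclusion rests on the two-sided 5% alpha carrying over from the Focal calculation, which the agreement with 3.9 supports. The error is definite but its reach is small: it misstates the sensitivity of one exploratory comparison and leaves the primary outcome, its power and recruitment as they are.

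**What to change.** In the Revised part of the sample size section, replace 3.4 with 3.8 points, keeping SD 7, correlation 0.6, 20% attrition and 80% power. It would help to state the two-sided 5% alpha and the method (t-based) in the same sentence, so that both Partner figures can be reproduced. If the authors did mean to assume complete follow-up of Partner children, they should say so and withdraw the claim that the assumptions are unchanged; 3.4 would then be correct for that case.

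The cost is one number, and a stated sensitivity that is slightly less favourable. No further schools or children are needed.

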### Statistical analysis plan

Statistical analysis will primarily be conducted in Stata/MP v18 [35] or later, unless specified otherwise. All analyses will be conducted just once at the end of the trial follow-up period, according to precise specifications detailed in a Statistical Analysis Plan (SAP) that will be approved by the TMG and TSC prior to the end of follow-up. Any departures from the analysis plan will be reported and justified in the final trial reports and other relevant published articles.

The flow of clusters and participants through the study will be presented according to CONSORT guidance for cluster RCTs. Continuous characteristics will be summarised in terms of the available sample size, arithmetic mean, standard deviation, median, interquartile range, minimum and maximum. Categorical characteristics will be summarised in terms of frequencies and percentages.

For all between group comparisons, clusters and participants (both Focal and Partner) will be analysed as part of the groups to which they were randomised, regardless of subsequent engagement with the allocated treatment. All analyses estimating between group contrasts will include all participants with data available for the relevant outcome (unless explicitly stated otherwise in the SAP). Point estimates of contrasts between randomised groups will be reported together with appropriate 95% confidence intervals. Point and interval estimates will be reported on the scale of the original measurements (as well as the scale used for the analysis should these differ). P-values for statistical tests will be two-sided unless specified otherwise in the SAP.

### Baseline data participants

Baseline data for the participating focal children will be summarised descriptively by randomised group and overall, according to the principles outlined above. Two sets of tables will be reported: one set including all randomised Focal children and another including just the subset of Focal children included in the primary analysis model. Baseline data for the participating Partner children will be summarised similarly in a separate set of tables. No formal comparison of baseline data between randomised groups will be undertaken (for either Focal or Partner children).

### Primary outcome analysis (focal children)

The planned primary analysis model will include all available post-randomisation TPS [26] scores as outcomes, modelling these measurements using a linear mixed effect model. This model will include fixed effects for treatment group, time point, and their interaction, and will also condition on fixed effects for baseline TPS mean composite score, year group, child FSM status, geographical location of school, and school level random intercepts. Correlation between repeated measurements within participants will be modelled using an unstructured covariance matrix for the model residuals. Precise details of the terms included in the model will be provided in the SAP (including plans for dealing with any incomplete baseline covariate data). If the fit of the planned primary analysis model is reasonable (see below), then the fitted model will be used to estimate differences (Intervention – Control) in expected TPS scores at both post-randomisation time points, together with 95% confidence intervals and p-values for tests of H_0_: $$\delta$$ = 0 (where $$\delta$$ is the difference in expected score at the relevant time point).

The appropriateness of key model assumptions will be checked using diagnostic plots based on the standardised residuals from the fitted model. If these plots (or indeed other extra-data considerations) suggest the observed data show important departures from the assumptions of the planned analysis, then we will undertake semi-parametric analyses of the scores at each post-randomisation time point in isolation. This will be accomplished using cumulative probability models based on ordinal regression [36]. The ordinal regression models will include fixed effects for treatment group, baseline TPS [26] mean composite score, year group and child FSM status, and a random intercept for school.

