#### Child consent procedure

All parents will be given the option to speak to a member of the research team or to contact the Chief Investigator in the event of additional questions. Consent to enter the study will be sought from each participant only after a full explanation has been given, an information leaflet offered and time allowed for consideration.

Participation in the study will be entirely voluntary and written informed consent from parents/carers will be obtained before child baseline data is collected and randomisation is conducted. On the consent form, parents/carers will be requested to consent for their child’s school to provide data including child’s name, date of birth, gender, home postcode, ethnicity, religion/belief, English as an additional language (EAL), education, health and care plan (EHCP) status, help received from a Speech & Language Therapist and/or an Educational Psychologist and receipt of Pupil premium and/or free school meals (FSM, a proxy for deprivation) for the purposes of sample description and potentially for use as covariates in analyses. The consent form for Focal children will also request parent/carers to provide their educational qualifications, employment status, ethnicity and consent/commitment to complete the EQ-5D-Y (proxy version 1), CHU-9D, and resource use data questionnaires at specified time-points. Parents/carers will return completed consent forms to the school.

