### Sensitivity analyses (Focal children)

Several additional planned analyses of the primary outcome will be undertaken to investigate the sensitivity of the results of the primary analysis to departures from the key statistical assumptions that underpin this analysis. In particular, we will investigate the impact that various alternative adjustment sets have on the results of the primary analysis, investigate the potential impacts of departures from the planned schedule of assessments, and undertake analyses of the primary outcome under different assumptions about any missing primary outcome data.

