### Data management

#### Data collection, management and verification

The five primary sources of quantitative data for this trial are:Data collected by research assistants during school visits at baseline, 15–20 weeks and 35–40 weeks. The TPS and ERRNI will be audio recorded, with these recording being subsequently scored, and the relevant data entered into the REDCap database. All of the other Research Assistant completed measures (CELF-5, Droodles and Communication Test) will be entered into the REDCap database after testing.Data collected from the teachers of participating focal children at baseline, 15–20 weeks and 35–40 weeks (CCC-2 and SDQ). These data will be collected via online Qualtrics surveys sent directly to teachers of participating focal children.Data collected from the parents of participating focal children at baseline, 15–20 weeks and 35–40 weeks. Parent/household demographic data (e.g. parent/carer employment, parent/carer ethnicity etc.) are collected as part of the paper consent forms completed by parents of participating focal children. These forms are returned to the research team who enter these into the REDCap database. Parent completed data for the economic evaluation (i.e. EQ-5D-Y, CHU-9D and resource use) will be collected electronically (via direct entry into the trial REDCap database), or via paper questionnaires (which are subsequently returned to the trial team and entered into the trial database)Data collected directly from the schools of participating children at baseline (provided for both focal and partner children). These data (e.g. age, gender, ethnicity etc.) are entered into password protected spreadsheets by school staff (one for each school). These are then securely shared with the research team.Data collected by research assistants during intervention fidelity assessments.

Monitoring data: E-PLAYS-2 software will record the content, duration and number of intervention sessions each child receives using a unique login ID. Access to the E-PLAYS information is password protected and will be accessed on University computers with Bitlocker Windows security. Data within the E-PLAYS software is anonymised.

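### The primary model adjusts for year group but not exact age, although date of birth is collected; adding age would be a small, nearly free gain in precision

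*Protocol article*

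**What the plan says.** The protocol article (Primary outcome analysis, focal children) specifies a linear mixed model with treatment, time point and their interaction and random intercepts for school. The model "will also condition on fixed effects for baseline TPS mean composite score, year group, child FSM status, geographical location of school". Age is not on the list. The same paragraph adds: "Precise details of the terms included in the model will be provided in the SAP". The ordinal fallback keeps baseline TPS, year group and FSM status but drops location.

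Year group has two levels: "Pupils will be recruited from Years 1 and 2" (Sample size calculations, Original).

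Exact age will be available. Under Child consent procedure, parents agree that schools "provide data including child’s name, date of birth, gender, home postcode", with other items, for describing the sample and "potentially for use as covariates in analyses". The data management section, describing baseline data from schools on both Focal and Partner children, says: "These data (e.g. age, gender, ethnicity etc.) are entered into password protected spreadsheets by school staff". Randomisation follows baseline data collection.

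The target difference of 2 TPS points is described as "a third of a year’s progress based on the standardisation sample given in the TPS manual".

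**The concern.** The plan uses growth with age to justify its target difference, yet enters age only as a two-level factor. If 2 points is a third of a year, one year is 6 points. Year group separates the two 12-month bands but not children within a band, who can be almost 12 months apart. Whatever part of that spread baseline TPS does not capture stays in the residual of the treatment comparison.

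What is at stake is precision only. Age is fixed before randomisation and schools are randomised, so leaving it out does not bias the treatment effect. Precision has some value here: the revised design has 85.2% power where the original aimed for 90%, and the Partner comparison rests on about 88 × 0.8 ≈ 70 analysed children.

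**Working it through.** **Inputs from the protocol (Sample size calculations).** Difference 2; SD 7 (variance 49); pre-post correlation r = 0.6, against 0.79 observed in the feasibility trial at 35–40 weeks; ICC 0.05; 44 schools per arm; 4.55 children per school; 20% attrition; two-sided 5% test.

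**Assumptions, because the documents give no figures.** Age is uniform over 12 months within each year group; the two year groups are equal in size; the slope on age is linear and the same at baseline and follow-up. The slope is 6 points per year (from the target difference), with 3 as a lower alternative.

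**Step 1: the plan's own figure.**
- Children analysed per arm: 44 × 4.55 × 0.8 = 160.2.
- Design effect: 1 + (4.55 × 0.8 − 1) × 0.05 = 1.132.
- Effective n per arm: 160.2 / 1.132 = 141.5.
- Residual variance: 49 × (1 − 0.6²) = 31.36.
- SE = √(2 × 31.36 / 141.5) = 0.666. Power = Φ(2/0.666 − 1.96) = 85.2%, as stated.

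**Step 2: size of the age component.** At 6 points per year the within-year age variance is 6²/12 = 3 (SD 1.73), and the between-year variance is 6² × 0.25 = 9.

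**Step 3: gain if SD 7 and r = 0.6 are overall values, not yet adjusted for year group.**
- Baseline TPS and year group: variance 49 − 9 = 40; covariance 29.4 − 9 = 20.4; residual 40 − 20.4²/40 = 29.6.
- Baseline TPS and exact age: variance 37; covariance 17.4; residual 37 − 17.4²/37 = 28.8.
- Reduction 2.6%. SE 0.647 against 0.638; power 87.1% against 88.0%. On 88 × 4.55 ≈ 400 children, 2.6% is about 11 children.

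**Step 4: gain if SD 7 and r = 0.6 are already net of year group.**
- Variance of age not explained by baseline TPS: 3 − 3²/49 = 2.816.
- Its covariance with follow-up TPS: 3 × (1 − 0.6) = 1.2.
- Variance removed: 1.2² / 2.816 = 0.51. The residual falls from 31.36 to 30.85, which is 1.6%.
- Power goes from 85.2% to 85.7% (a gain of 0.57 points before rounding). A simulation of 1,000,000 children gave the same reduction (31.39 to 30.87).

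**Step 5: range.** Each cell gives the reduction in residual variance and the change in power.

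| Slope (points/year), r | SD and r overall | SD and r net of year group |
|---|---|---|
| 6, r = 0.6 | 2.6%; 87.1% to 88.0% | 1.6%; 85.2% to 85.7% |
| 6, r = 0.79 | 1.2%; 97.8% to 97.9% | 0.8%; 97.5% to 97.6% |
| 3, r = 0.6 | 0.4%; 85.6% to 85.7% | 0.4%; 85.2% to 85.3% |
| 3, r = 0.79 | 0.2%; 97.56% to 97.58% | 0.2%; 97.50% to 97.52% |

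The starting powers above 85.2% in the overall column at r = 0.6 arise because that reading credits year group with some variance as well. They do not correct the plan's figure.

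**The case against.** The strongest case against raising this has five parts.

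- **The SAP.** Exact model terms are deferred to the SAP, which is not shown, and among the sensitivity analyses "we will investigate the impact that various alternative adjustment sets have on the results of the primary analysis". The SAP may well add age. Still, the article commits to a named list without it, and a sensitivity analysis does not sharpen the primary estimate.
- **Size.** The gain is under one percentage point of power in every case. The uncertainty in the planning SD (7.2, 95% CI 5.4 to 9.7) matters far more. This stands.
- **Slope.** Six points per year comes from the test's standardisation sample, not from children selected for social communication difficulties. The sample size section, when discussing clustering, also expects little difference between the two consecutive years. A flatter slope moves the result towards the 0.2 to 0.4% rows. This stands.
- **Role of year group.** The sample size section treats it as a level of the design, so it need not be meant as a measure of age. This stands, and is a reason to keep it.
- **Reach.** The ordinal fallback does not use an identical list, and the secondary and Partner models are described only as similar. So it cannot be said that one fixed list runs through all models. Only the CACE analyses are tied to the primary model's baseline covariates.

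A reader might infer from 6 points per year that a 6-point spread, three times the target difference, is left in the residual. It is not. Six points is the raw gap between the oldest and youngest child in a year group. The within-year SD is 1.73, and baseline TPS absorbs most of it. If baseline TPS captured none of the age effect, the full variance of 3 would come out of 31.36 and power would reach 88.5%. That is not realistic, because a child's baseline score already reflects the child's age.

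**Conclusion.** The point holds as a minor improvement. The named adjustment set leaves out exact age, which will be in hand before randomisation. At r = 0.6 and 6 points per year this costs about 1.6 to 2.6% of residual variance, or 0.6 to 0.9 percentage points of power. At r = 0.79 or 3 points per year it costs 0.2 to 1.2%, or at most about 0.15 points. The width of the first range reflects whether the planning SD and correlation are read as overall values or as net of year group, which the protocol does not say. All figures rest on the assumed uniform ages and linear, parallel slope. The documents give neither the age slope in Focal children nor the association of age with follow-up TPS given baseline.

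The documents do not support a claim of bias, of an invalid primary analysis or of an error in the stated 85.2%, which does not use age or year group.

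**What to change.** Keep year group and add baseline age in months as a continuous fixed effect in the primary model. Do the same in the ordinal fallback and in the CACE, secondary outcome and Partner models, naming the term in each so that the adjustment sets are explicit. This takes one line in the SAP per model, needs no new data and costs one degree of freedom in each model.
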